**Methods/design:**

A total of 408 patients will be enrolled from five endoscopic centers. Patients will be divided into two groups: (1) group A, which is the EUS regular needle group (EUS-FNA) and (2) group B, which is the EUS ProCore needle group (EUS-FNB). Patients in group A will be examined with a 22G EchoTip Ultra needle, and patients in group B, with a 22G EchoTip ProCore needle. For all included patients, four EUS-guided passes will be made in each lesion. In the first and second pass, a slow-pull suction method of the stylet will be done. The third and fourth pass will use manual suction of 5 cc. The primary objective is to compare the diagnostic yield of malignancy by EUS-FNA versus EUS-FNB.

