**Fig. 1 Fig1:**
[figure not shown]
CONSORT flowchart illustrating the randomization and recruitment process in the study. ^1^ Each slide will be assessed by two independent experts. The cytologists and pathologists will follow the protocol to assess the samples and will be blinded as to which technique is used for which specimen. ^2^ If diagnostic failure occurs, the patient will be allowed to crossover to the other group after agreeing to accept a needle biopsy again on the same lesion 1 week later. ^3^ Three follow-up points are scheduled after the biopsy (1-week postoperational follow-up, 12-week follow-up, and 48-week follow-up); thereafter, the follow-ups will be conducted via telephone interviews or outpatient interviews. Once the surgical pathologic results are obtained, we will stop the follow-up

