### Interventions

Patients will be allocated randomly into group A (EUS-FNA, n = 204) or group B (EUS-FNB, n = 204). Group A patients will be examined with the 22G EchoTip Ultra needle, and group B will be examined with the 22G EchoTip ProCore needle.

The procedure will be performed under deep sedation according to the principles of “monitored anesthesia care.” The patients will be anesthetized with intravenous administration of propofol by trained anesthetists. All patients will receive oxygen during the procedures; blood pressure and heart rate will be monitored. Once the lesion is evaluated by EUS, the echoendoscopist will select the shortest pathway, while avoiding blood vessels, to reach the lesion. Under real-time visualization, each lesion will be punctured with four needle passes. To eliminate technical biases, the same procedure for obtaining samples will be applied to each patient undergoing EUS-FNA or EUS-FNB.

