### Technique for EUS-FNA and EUS-FNB

**1) The first and second needle passes (slow pull)** [20]: The needle will be advanced into the lesion under real-time EUS visualization. Back and forth movements will be made 20 times within the lesion and will be performed using simultaneous minimal negative pressure by pulling the needle stylet slowly and continuously.

**2) The third and fourth needle passes (5-ml suction)** [18]: After the needle has been advanced into the lesion under real-time EUS visualization, the stylet will be removed. Continuous suction will be applied with a 5-ml syringe, and the needle will be moved back and forth 20 times within the lesion. Suction will be released, and then, the needle will be withdrawn from the lesion.

After biopsy, the samples will be labeled immediately with numbers in the order of the needle pass. Samples will be prepared for histological and cytological examinations. The cytologists and pathologists will always be blinded regarding which technique was used for which specimen.

After the selected lesion has been punctured during the four needle passes, if no core tissue is obtained or if the operators determine the specimens are insufficient according to the results of the macroscopic onsite evaluation (MOSE) [21], the operators will use a proper puncture method to obtain samples as the backup procedure.

If diagnostic failure occurs, the patient will crossover to the other arm after agreeing to accept a needle biopsy again on the same lesion 1 week later with the same method mentioned above.

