### Assessment standards

After patient recruitment is completed, all samples will be reassessed by selected cytologists and pathologists from Tongji Hospital, Tongji Medical College, HUST, and from the Cancer Institute & Hospital, Chinese Academy of Medical Sciences, Peking Union Medical College. They will assess the samples following the protocol and remain blinded regarding which technique was used for which specimen. Each sample will be assessed by two independent experts. If the two experts have different judgments, they should discuss it together and make a final decision [7].

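### Samples are numbered by needle pass and the pass fixes the sampling method, so a pass number left visible at reading would break the stated blinding to technique for the slow-pull versus suction comparison

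*Protocol article*

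**What the plan says.** Under Technique for EUS-FNA and EUS-FNB, the protocol article sets out four passes per lesion in a fixed sequence: "The first and second needle passes (slow pull") and then "The third and fourth needle passes (5-ml suction"). The Abstract repeats the order: "In the first and second pass, a slow-pull suction method of the stylet will be done". The Interventions section makes it common to both arms: "the same procedure for obtaining samples will be applied to each patient undergoing EUS-FNA or EUS-FNB".

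The labelling rule follows: "After biopsy, the samples will be labeled immediately with numbers in the order of the needle pass". Shortly afterwards, in the same paragraph, comes the blinding statement: "The cytologists and pathologists will always be blinded regarding which technique was used for which specimen". Assessment standards says the same of the central readers, who are to "remain blinded regarding which technique was used for which specimen", and so does the legend of Fig. 1.

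Secondary objective 4 (Objectives section) compares sample quality between slow-pull and suction. The Data analysis section applies McNemar's test to three-level grades of blood contamination and cellularity for that comparison. Tissue integrity is also graded A to C under the histology criteria, although Data analysis does not name it for this comparison.

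**The concern.** If the technique can be worked out from the pass number, and the pass number is the sample's label, a reader who sees the label and knows the sequence is not blinded to technique.

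This matters because the outcomes of objective 4 are graded by readers. Blood contamination depends on the share of the slide covered, with cuts at 25 % and 50 %, and a slide near a cut can be placed on either side. The Discussion section records the expected result in advance: suction should give more cells but also more blood. A reader who knows the method and shares that expectation could shift borderline grades in one predictable direction. A within-patient test counts such shifts as a difference between methods. Having two experts who settle disagreements by discussion does not protect against this if both see the same label.

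**Working it through.** The plan states no figure on this point, so the check is to set its statements side by side.

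1. **From pass to technique.** The Abstract and the Technique section give passes {1, 2} → slow-pull and {3, 4} → suction. Nothing in the article randomises or varies the order. The Interventions section applies the same procedure to each patient in both groups.

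2. **From label to pass.** The Technique section numbers samples in pass order, so the label is the pass number.

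3. **Combined.** Label 1 or 2 means slow-pull and label 3 or 4 means suction, with probability 1 in every patient.

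4. **What readers may be assumed to know.** The Fig. 1 legend says: "The cytologists and pathologists will follow the protocol to assess the samples". The sequence is a prominent design feature, given even in the Abstract. This makes it likely, though not certain, that readers know it.

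5. **Search for a safeguard.** The article describes no recoding of slides or blocks, no covering of labels and no randomised reading order.

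6. **Number of samples concerned.** 408 patients × 4 passes = 1,632 planned samples: 408 × 2 = 816 slow-pull and 816 suction. Backup and crossover samples are not counted.

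7. **Does the label reveal the needle?** Both arms use labels 1 to 4 for the same sequence, so the label carries no information on EUS-FNA versus EUS-FNB. The randomised comparison and the primary endpoint (diagnostic yield of malignancy by needle) are not unblinded by this route.

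8. **Can the bias be sized?** Let *b* be the share of slides that lie near a grade boundary and *s* the share of those that a reader moves in the expected direction. The spurious shift, as a proportion of all slides of one method, is *b* × *s*. The documents give neither quantity, so no figure follows.

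**The case against.** **The label at reading may not be the label at biopsy.** Numbering at the bedside is needed for traceability. The article does not say which identifier the prepared slides carry, and a condensed article may leave slide accessioning to the full protocol. This stands. A reader might infer that blinding to technique is absent altogether, but the documents do not support that: they show a conflict that holds only if the pass number remains visible. It is still more than missing detail, because a labelling rule and a blinding claim that do not fit together are both stated, with nothing between them to reconcile them.

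**Technique may mean the needle.** The section heading uses the word for EUS-FNA and EUS-FNB, and elsewhere slow-pull and suction are called approaches or methods. On that reading the label gives nothing away. However, the blinding is stated specimen by specimen, and needle type is constant across a patient's four initial passes, so the wording fits slow-pull versus suction better. If the needle alone were meant, the article would state no reader blinding for objective 4, and the remedy would be the same.

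**Readers follow the protocol only for grading.** That is possible. It makes knowledge of the sequence less certain, but it does not keep the sequence from them.

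**The grades have anchors.** They do: a 550-micron minimum for Grade A tissue, cluster and cell counts for cellularity, and area cuts for blood. Anchors and double reading reduce discretion but do not remove it near a boundary.

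**A size might be assumed.** One might suppose that moving 10 % of borderline slides gives a 10-point false difference. It does not. Ten per cent of a subset is 0.10 × *b* of all slides, which is below 10 points unless every slide is borderline, and the 10 % itself has no source in the documents.

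**Conclusion.** The point holds in a limited form. As written, numbering by pass conflicts with the stated blinding to technique whenever the pass number can be seen at reading. This rests on two assumptions: that no recoding takes place before reading, and that technique in the blinding statement includes slow-pull versus suction.

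The consequence is a possible directional expectation bias in secondary objective 4: the blood contamination and cellularity grades, and any tissue-integrity comparison of the two methods. Its size is unknown. A reader might infer that the main result of the trial is compromised. The documents do not support this, because the label is silent on needle type.

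A separate limit applies to the same objective. Slow-pull always comes first, so the suction passes always enter a lesion already punctured twice. Technique and pass order are completely confounded, and blinding the readers cannot separate them.

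**What to change.** - Keep the pass number in the case report form. Before the central reassessment, give every slide and block a random code that does not carry pass order, and cover or replace the existing label.
- Present the slides in random order.
- Have someone who does not read samples hold the key linking code to patient and pass until the grades are locked.
- Name these masked central readings as the source of the grades for objective 4.
- Say in the blinding statements whether technique means the needle, the sampling method or both. If recoding is already done, one sentence stating so settles the conflict.
- State with objective 4 that technique is confounded with pass order, that recoding does not remove this, and that the comparison is to be interpreted within that limit.

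The cost is a small relabelling task and a linkage file for up to 1,632 pass samples (slides and blocks may be more numerous). No extra reader, procedure or patient is needed. Assessment standards places the central reassessment after recruitment is completed, and Trial status reports 372 of 408 patients enrolled with recruitment still open. At that date the change could therefore still cover every patient.

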### Assessment standards

After patient recruitment is completed, all samples will be reassessed by selected cytologists and pathologists from Tongji Hospital, Tongji Medical College, HUST, and from the Cancer Institute & Hospital, Chinese Academy of Medical Sciences, Peking Union Medical College. They will assess the samples following the protocol and remain blinded regarding which technique was used for which specimen. Each sample will be assessed by two independent experts. If the two experts have different judgments, they should discuss it together and make a final decision [7].

#### Histology assessment criteria

The histological assessment will involve the following:Tissue integrity assessment [20, 22]Grade A: core tissue (an architecturally intact piece of tissue measuring at least 550 micron in greatest axis, as the diameter of a high-power microscopic field), clearly characterizes the lesion sufficient for diagnosisGrade B: core fragments present, tissue does not meet the criteria for architecturally intact histology but can still yield a diagnosis based on cell morphologyGrade C: no lesion tissue found and cannot yield a diagnosisBlood cell contamination assessment [18]Grade A: little blood contamination, minimal surface area (SA) < 25 % of slideGrade B: medium blood contamination, 25–50 % of the slideGrade C: much blood contamination, SA > 50 % of the slide

#### Cytology assessment criteria

The cytological assessment involves the following:Cellularity assessment [9]Grade A: satisfactory, more than four clusters, with a minimum of ten cells in each clusterGrade B: adequate, approximately two to four clusters, with a minimum of ten cells in each clusterGrade C: unsatisfactory, fewer than two clusters, or no cellular smearBlood cell contamination assessment [18]Grade A: little blood contamination, SA < 25 % of slideGrade B: medium blood contamination, 25–50 % of slideGrade C: much blood contamination, SA > 50 % of the slide

### Collecting data

Table 1 shows the types of data collected and when the data should be collected.

**Table 1 Tab1:** Study schedule for data collection

Item	Interview 1	Interview 2	Interview 3	Interview 4
	1-0 week before EUS	0-1 week after EUS	12 weeks ± 5 days after EUS	48 weeks ± 5 days after EUS
Informed content	X			
Inclusion criteria	X			
Patient characteristics	X			
Blood routine tests	X	X		
Coagulation routine tests^1^	X			
Blood biochemistry tests^2^	X	X		
Blood tumor markers tests^3^	X		X	X
Complications		X	X	X
Clinical signs^4^	X	X	X	X
Imaging examination	X	X	X	X
Cytology examination		X		X
Pathology examination		X		X
Surgical-pathological examination		X	X	X
Therapies		X	X	X

^1^Coagulation routine tests: prothrombin time (PT), activated partial thromboplastin time (APTT), thrombin time (TT), fibrinogen, INR

^2^Blood biochemistry tests: AST, ALT, BUN, Cr, ALP, lipase, amylase

^3^Blood tumor marker tests: CEA, CA19-9, CA72-4, AFP, SSC, NSE

^4^ Clinical signs include pain, weight loss, cachexia, etc.

### Final diagnosis

The reports will be stratified into four diagnostic categories for the histological and cytological evaluation, including “positive for malignancy,” “suspicious for malignancy,” “atypia,” and “negative for malignancy.” The “positive for malignancy” will be considered if the reports contain words such as “diagnostic for malignancy,” “compatible with carcinoma,” “consistent with adenocarcinoma,” “positive for malignant cells,” “malignant cells present,” or when specified by the exact tumor type [23]. The “positive for malignancy” will not be considered if the reports contain words such as “suspicious for malignancy,” “atypia,” or “negative for malignancy.”

#### Final diagnostic criteria

The final diagnostic criteria [20] include the following:For patients who undergo surgery, the final diagnoses will be based on the definite histological diagnoses from surgical resection specimens.In the absence of surgical pathology, a minimum 48 weeks of clinical follow-up time will be conducted. If the lesion spontaneously resolves or has no sign of deterioration in follow-up imaging studies, the lesion will be considered a benign disease. If the lesion shows enlargement or metastasis, and the patient presents malignant symptoms such as weight loss, anemia, or dies of tumor complications during the follow-up, the lesion will be considered a malignant disease.

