### Objectives

The primary objective of this study is to compare EUS-FNA versus EUS-FNB for the diagnostic yield (%) of malignancy [13]. The secondary objectives are to compare EUS-FNA versus EUS-FNB for 1) the overall diagnostic yield (%) from solid lesions; 2) the diagnostic yield (%) from pancreatic and nonpancreatic solid lesions, 3) the crossover diagnostic yield (%), and 4) the sample quality obtained by either the slow-pull or suction approaches, respectively.

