### Statistical analysis

#### Sample size

We assumed that the diagnostic yield of malignancy for EUS-FNA was 80 % [23] versus 93 % for EUS-FNB [11, 13]. Because approximately 70 % of patients are expected to be diagnosed with malignancy [9], the sample size should be 342, with a power of 85 % and a two-sided significance level of 5 %. Considering 20 % of patients will be lost to follow-up, the estimated patient number in this trial should be 408.

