## Discussion

The role of EUS-FNA in obtaining cytological materials is well-established [24]. However, a recent study suggests the false positive rate of FNA cytology is 5 % to 7 %, which is higher than the originally reported rates of 0 % to 1 % [25, 26]. Moreover, an increased interest in histological tissue sampling under real-time EUS imaging exists because of the advantage in diagnosing certain suspected tumor types, such as neuroendocrine tumor and lymphomas [27]. A standard 19G FNA needle has been used to obtain histological materials and achieved a diagnostic accuracy of 94.5 % [28], although the device is highly associated with technical failures. A Quick-Core needle was used with an overall diagnostic accuracy of 75 % to 84 % [29, 30]. One drawback of the Quick-Core needle is that it is difficult to maneuver, especially for transduodenal biopsy. Recently, a new 22G needle with a reverse bevel at the tip (EUS-FNB) has become available. The ProCore needle design combines the features of an FNA needle with a core biopsy needle [20], which has enhanced flexibility, especially for core tissue collection. Results from a multicenter study on EUS-FNB showed that, overall, the operations were completed in 98.24 % patients, the histological specimens were adequate in 89.47 % patients, and the diagnoses were accurate in 92.9 % patients [11]. EUS-guided tissue acquisition now seems to be more suitable for histological evaluation [13, 20]. Here, we carry out a randomized controlled trial to compare the diagnostic efficiency of EUS-FNB versus EUS-FNA and to assess the sample quality obtained by different types of needles with different methods. To our knowledge, this is the largest cohort study on EUS-FNB so far. The outcome measurements will help us to understand the special indications for each technique and their diagnostic accuracy. In addition, Aadam et al. reported a significant rescue effect of FNA crossover to FNB [13]. We specifically designed our trial to allow the patient to crossover to the other arm if diagnosis is not achieved after the first round of needle biopsy, which will help us draw our conclusions.

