Some limitations exist in the present study design. For instance, we will not be performing the rapid onsite evaluation (ROSE) in the current trial. ROSE is most frequently used in the United States, and the absence of an onsite cytopathologist has been shown to affect the diagnostic yield by increasing the number of inadequate samples. Although its popularity is growing here in China as well, several alternative strategies, including the macroscopic onsite evaluation (MOSE), have been reported to improve the diagnostic yield [21]. The well-trained endoscopists in our centers will apply MOSE and gross inspection to evaluate the quality of the specimens. Second, although the crossover design is critical, obtaining agreement from the patients for the second biopsy may be difficult because it may increase the risk of complications. Consequently, the number of patients recruited may be reduced, thereby leading to suboptimal conclusions. Third, some patients may not undergo surgery and, hence, will not have any final pathology report. In addition, the possibility exists that contact with the patient will be lost during the 48 weeks of follow-up. To prevent dropout, local research assistants will be recruited to help complete the patient registration information (record at least two phone numbers) and ensure that appointments are being made for follow-up assessments.

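### The non-surgical final-diagnosis rule labels a treated, stable cancer benign and leaves symptom-free progression unclassified, so the primary yield's denominator is misclassified by an unknown amount and in an unknown direction

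*Protocol article*

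**What the plan says.** The primary objective (Objectives) is to "compare EUS-FNA versus EUS-FNB for the diagnostic yield (%) of malignancy".

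Final diagnostic criteria sets the reference standard. For patients who have surgery, "the final diagnoses will be based on the definite histological diagnoses from surgical resection specimens". For the others, "In the absence of surgical pathology, a minimum 48 weeks of clinical follow-up time will be conducted", and two rules apply:

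- Benign: "If the lesion spontaneously resolves or has no sign of deterioration in follow-up imaging studies, the lesion will be considered a benign disease".
- Malignant: "If the lesion shows enlargement or metastasis, and the patient presents malignant symptoms such as weight loss, anemia, or dies of tumor complications" during follow-up.

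A biopsy report that is positive for malignancy (Final diagnosis) is not a listed ground for the final diagnosis. Table 1 records therapies at Interviews 2, 3 and 4, but the rules do not use them. The Discussion accepts that "some patients may not undergo surgery and, hence, will not have any final pathology report".

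Sample size assumes that "the diagnostic yield of malignancy for EUS-FNA was 80 % [23] versus 93 % for EUS-FNB", and that about 70 % of patients will have malignancy.

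**The concern.** The two non-surgical rules fail in different ways.

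1. In the benign rule, the word about spontaneous course qualifies only resolution. The second limb, absence of deterioration, stands alone. A cancer proven by biopsy, not resected, and stable or shrinking on therapy meets it and is called benign. The protocol says tissue sampling has an "advantage in diagnosing certain suspected tumor types, such as neuroendocrine tumor and lymphomas", and such tumours could plausibly be stable or respond without resection.
2. The malignant rule joins two requirements. A lesion that enlarges, or even metastasises, without symptoms or tumour death is neither malignant nor benign.

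The first failure removes true positives from numerator and denominator together. The second can remove missed cancers from the denominator. Both act on the primary endpoint, and both can depend on what the biopsy showed, because the biopsy may influence treatment.

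**Working it through.** **Step 1: which denominator is planned.** Inputs from Sample size: 80 % and 93 %, power 85 %, two-sided 5 %, 70 % malignant. With unpooled variance:

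n per arm = (0.80×0.20 + 0.93×0.07) × (1.960 + 1.036)² / 0.13² = 119.59

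Two arms need 239.2 malignant patients, and 239.2 / 0.70 = 341.7, which rounds up to the stated 342. Dividing by 0.70 makes sense only if the yield is taken over patients with malignancy. The final-diagnosis rule therefore decides who is counted.

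**Step 2: model.** Let p be the true yield, r the share of true positives relabelled benign, and u the share of missed cancers left unclassified and dropped. Then

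observed yield = p(1−r) / [p(1−r) + (1−p)(1−u)]

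The documents give neither r nor u; all values below are assumptions. Resected patients are classified by histology, so r cannot exceed the unresected share of true positives.

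**Step 3: crossover.** On diagnostic failure a patient who agrees is re-biopsied with the other needle. Let c be the uptake, and assume the second needle detects at the protocol's own yield q (93 % after FNA, 80 % after FNB) and that these patients are relabelled at the same r. Then, with u = 0, the missed cancers left in the denominator are (1−p)(1−c·q·r).

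Example, r = 20 %, c = 1:
- FNA: 0.80×0.8 = 0.640; missed 0.20×(1−0.93×0.2) = 0.1628; yield 0.640/0.8028 = 79.7 %.
- FNB: 0.93×0.8 = 0.744; missed 0.07×(1−0.80×0.2) = 0.0588; yield 0.744/0.8028 = 92.7 %.

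**Step 4: results.**

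| r | u | c | FNA | FNB | Difference (points) |
|---|---|---|---|---|---|
| 0 | 0 | 0 | 80.0 % | 93.0 % | 13.0 |
| 10 % | 0 | 0 | 78.3 % | 92.3 % | 14.0 |
| 20 % | 0 | 0 | 76.2 % | 91.4 % | 15.2 |
| 40 % | 0 | 0 | 70.6 % | 88.9 % | 18.3 |
| 20 % | 0 | half | 77.9 % | 92.0 % | 14.1 |
| 20 % | 0 | all | 79.7 % | 92.7 % | 13.0 |
| 0 | 20 % | 0 | 83.3 % | 94.3 % | 11.0 |
| 20 % | 20 % | 0 | 80.0 % | 93.0 % | 13.0 |

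**Step 5: power.** With 342 evaluable patients (342×0.70/2 = 119.7 malignant per arm) and a pooled chi-square test, power is 84.2 % without misclassification. It is 83.2 % at r = 20 %, u = 0; 76.3 % at r = 0, u = 20 %; and 75.3 % with both at 20 %, where the denominators shrink to 95.8 per arm although the yields look right.

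**The case against.** The strongest reply is that the gap is one of wording and its effect on the result is unproven. Much of that stands.

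- A reader might infer that missed cancers go untreated, progress and stay in the denominator, so that the rule must widen the difference in favour of FNB. The documents do not support this. Technique for EUS-FNA and EUS-FNB provides re-biopsy with the other needle one week after a diagnostic failure, and at full uptake the distortion in the table disappears. Uptake is unknown; the Discussion warns that agreement may be hard to obtain.
- The unclassified group works in the opposite direction, so no net direction follows.
- The relabelled share is assumed, and resected patients are exempt from it.
- A reader might also fear an inflated type I error. If the true yields are equal and the reclassified shares are equal, both arms shift alike; the harm then is to the estimate and the power.
- A biopsy that was right would appear as a false positive, but a false-positive rate is not among the stated objectives.

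It can also be said that the article condenses a longer document and that its criteria are introduced as a list that may not be complete. That does not remove the point. The article prints a definite rule, and as printed the rule gives the wrong class for treated disease and no class for symptom-free progression.

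**Conclusion.** The point holds as a misclassification of the primary denominator. Both defects follow from the text alone, and the reproduction of 342 shows that the denominator is patients with malignancy.

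The size and net direction are not established. Under the assumed shares examined, a true difference of 13 points could appear as anything from 11.0 to 18.3, or unchanged. These figures rest on the protocol's yields of 80 % and 93 %, on assumed values of r, u and crossover uptake, and on the inference that a positive biopsy influences treatment. A claim that the rule favours one needle goes further than the documents allow. By the same reasoning, the rule cannot be defended as conservative. Because it decides who counts in the primary endpoint, it should be corrected before final diagnoses are assigned.

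**What to change.** Amend the final-diagnosis rule for patients without surgical pathology, identically in both arms:

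1. Benign: no deterioration over the 48 weeks in a patient who received no anti-tumour therapy.
2. Malignant: metastasis, with or without symptoms; enlargement with symptoms or tumour death, as now.
3. Indeterminate: enlargement without symptoms or tumour death, and treated lesions without deterioration, whatever the biopsy showed.

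Analyse the primary yield twice, with all indeterminates counted first as malignant and then as benign. The biopsy result should not be used to resolve them: classing treated biopsy-positives as malignant while excluding treated biopsy-negatives would again tie the denominator to the test. The two results show sensitivity to the rule; they are not strict bounds on the true difference.

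Report beside this an analysis free of the reference standard: positive for malignancy at the first procedure, over all randomised patients, by arm.

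The cost is wording and two further analyses on data already scheduled, since therapies are recorded at Interviews 2 to 4 and imaging throughout. No imaging adjudication is needed; the two experts named under Assessment standards read samples, not scans. The downside is small: some patients will have no definite final diagnosis, and the primary result is shown with a range.
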